## Abstract

**Background:**

The Scottish Government set out its policy on addressing the poor oral health of Scottish children in 2005. This led to the establishment of Childsmile, a national programme designed to improve the oral health of children in Scotland. One element of the programme promotes daily tooth brushing in all nurseries in Scotland (Childsmile Core). A second targeted component (Childsmile Nursery) offers twice-yearly application of fluoride varnish to children attending nurseries in deprived areas. Studies suggest that fluoride varnish application can reduce caries in both adult and child populations. This trial aims to explore the effectiveness and cost-effectiveness of additional preventive value fluoride varnish application compared to Childsmile Core.

**Methods/Design:**

The Protecting Teeth@3 Study is an ongoing 2 year parallel group randomised treatment as usual controlled trial. Three-year-old children attending the ante pre-school year are randomised (1:1) to the intervention arm (fluoride varnish & treatment as usual) or the control arm (treatment as usual). Children in the intervention arm will have Duraphat® fluoride varnish painted on the primary tooth surfaces and will continue to receive treatment as usual: the core Childsmile Nursery intervention. Children in the treatment as usual arm will receive the same series of contacts, without the application of varnish and will also continue with the Childsmile Core intervention. Interventions are undertaken by Childsmile trained extended duty dental nurses at six-monthly intervals. Participants receive a baseline dental inspection in nursery and an endpoint inspection in Primary 1 at the age of 5 years old.

We will use primary and secondary outcome measures to compare the effectiveness of Duraphat® fluoride varnish plus treatment as usual with treatment as usual only in preventing any further dental decay. We will also undertake a full economic evaluation of the trial.

**Trial registration:**

This study is registered at ClinicalTrials.gov. Number: NCT01674933 (24 August 2012).

**Electronic supplementary material:**

The online version of this article (doi:10.1186/s12903-015-0146-z) contains supplementary material, which is available to authorized users.

## Background

This study will be performed according to the Research Governance Framework for Health and Community Care [6] and The Medicines for Human Use (Clinical Trials) Regulations [24]) SI 2004:1031 (as amended), and World Medical Association Declaration of Helsinki: Ethical principles for medical research involving human subjects 1964 (as amended). Amendment number 4, Protocol version V2.3, 31st July 2015. Duraphat has been considered to be an Investigational Medicinal Product for the purposes of this trial. The notification from the MHRA is shown in Additional file 1; the study has been given the EUDRACT number 2012-002287-26. All investigators and key trial personnel will complete biennial Good Clinical Practice training.

In 2005 the Scottish Government set out its policy on addressing the poor oral health of Scottish children. A series of reports had highlighted persistently high rates of dental caries with significant inequalities in oral health [16], low rates of NHS dental registration for young children (35 % of 0–2 year-olds in 2004) [17], and extremely limited preventive activity [18].

The 2005 Scottish Government Report “An Action Plan for Improving Oral Health and Modernising Dental Services in Scotland” announced what was to become the Childsmile oral health improvement programme [19]. The aim was to shift the balance of care towards more preventive and anticipatory care and target the early years in an attempt to promote health improvement from a young age. Programme development was founded on the principles outlined in the Ottawa Charter for Health Promotion [30].

Two Childsmile Demonstration Programmes were subsequently established in 2006, one in the East and one in the West of Scotland, with a targeted approach to improving the oral health of young children. Both were to run initially for 3 years, in order to allow the Programmes to evolve as a result of ongoing monitoring, evaluation, and stakeholder feedback. The Programmes complemented a national toothpaste/toothbrushing scheme set up a few years previously, whereby free toothpaste/toothbrush packs are distributed to every child in Scotland on at least six occasions during their first 5 years and free daily toothbrushing offered to every 3 and 4 years old child attending nursery schools in Scotland. The toothbrushing programme is also available to primary one and two children in schools situated in disadvantaged areas of National Health Service (NHS) Boards across the country. This programme, which became Childsmile Core, built on pre-existing local NHS Board-based toothbrushing initiatives, and enabled standardisation across the country with national procurement of the toothbrushing supplies and the publication and implementation of national standards for toothbrushing programmes [12, 13].

In nursery schools - the setting for the present study - Childsmile Core promotes daily tooth brushing, backed up with free dental packs containing fluoride toothpaste (circa 1000 ppm F), toothbrushes and advice leaflets, fruit and freely available water. Children in nurseries in deprived areas are also offered twice-yearly application of fluoride varnish from the time they start nursery under the Childsmile Nursery programme. In the period December 2006 to July 2011 168,000 Duraphat applications were completed under this programme, with no reported significant adverse events.

However, it is important to ascertain the additional preventive value fluoride varnish application in nursery schools may bestow over and above that gained from the Childsmile Core activities described above. There is some evidence from quasi-experimental data at the population level that the Childsmile Core intervention on its own has indeed improved the oral health of children in the Greater Glasgow area [2, 3]. The study will establish whether fluoride varnish will deliver benefits which are additional to those of the Childsmile Core Programme.

A systematic Cochrane Review of fluoride varnish application (Marinho et al. [9] concluded that this treatment reduced worsening of caries (known as a 'prevention fraction') in the primary dentition by 33 %, as measured by the 'd_3_mfs' score for deciduous teeth (number of decayed (at the dentine level), missing and filled surfaces). At the 'd_3_mft' level (decayed missing and filled teeth), the amount of prevented disease was possibly larger with an estimate of 53 %. Most of the studies included in the review were from populations with regular use of fluoride treatments, especially toothpaste.

On the one hand it is known that many deprived children in Scotland have not been using fluoride toothpaste in the past, but on the other hand the Childsmile programme should be addressing this problem. Perhaps a 33–53 % reduction in worsening of dmfs/dmft is a reasonable estimate of how much fluoride varnishes could achieve in a deprived population in the West of Scotland. However, the Cochrane review was only based upon nine trials, and only two of these looked at the deciduous teeth of 3 and 4 year olds. The 'numbers needed to treat' varied from 3.7 in low caries populations to 1.6 in higher caries populations.

A number of relevant studies have been published since the 2002 review. A randomised controlled trial by Skold et al. [21] involved Swedish schoolchildren being assigned different frequencies of varnish treatment, across three different levels of dental risk including a 'high risk' group. This study demonstrated a prevention fraction for varnish at six-monthly intervals of 69 % in high risk areas, 66 % in medium risk areas, and only 20 % in low risk areas. Although of great interest the study is of secondary school children aged 13 to 16 years, so does not answer the specific questions addressed in the present study. A German study reported by Borutta et al. [4]) appears to be closer to the proposed study. The aim was to assess the caries inhibition effect of fluoride varnishes among preschool children with high caries risk though an examiner-blind, clinically controlled 2-year study with 200 randomly selected 2- to 4-year-olds. As with the present study, four varnish applications were offered. The study reports a caries reduction level of 57 % for the fluoride varnish compared with controls. However there is no reference to the study taking place within an established prevention programme as represented by Childsmile Nursery in the present study.

A third RCT [7] investigated the preventive effect of fluoride varnish in primary school children aged around 7 years old. Randomisation was at the school year level with either Primary 2 or Primary 3 receiving fluoride varnish treatment. The percentage of children with increased caries was high in both intervention (53 %) and 'treatment as usual' group (50 %). Weaknesses in this study include the 'clustered within the same school' design (which could have encouraged compensatory action to improve dental health in control classes), blinding limited to the evaluator, and difficulties recruiting children with a high risk of caries.

A recent trial involving schoolchildren in the North West of England [10] also failed to find any evidence of effectiveness of fluoride varnish in a public health programme. However, the North West England trial was undertaken in older children (aged 7–8 years old), while the present study focuses on 3 and 4 year olds. In addition the small amount of varnish used in the North West England trial (3 applications of 22,600 ppm fluoride varnish per year for 3 years) applied to permanent molars may have been insufficient to provide effective dental caries prevention. Finally, the present study takes place within the Childsmile programme of supervised nursery toothbrushing for children from more deprived areas who may be more at risk of developing caries.

### Study rationale – hypothesis

In nursery schools - the main setting for the present study – the Scottish Government’s Childsmile Core programme promotes daily tooth brushing, backed up with free dental packs containing fluoride toothpaste (circa 1000 ppm F), toothbrushes and advice leaflets, fruit and freely available water. Children in nurseries in deprived areas are also offered twice-yearly application of fluoride varnish from the time they start nursery. It is important to ascertain the additional preventive value this may bestow over and above that gained from the Childsmile Core activities described above. The study will establish whether fluoride varnish will deliver benefits which are additional to those of the Childsmile Core Programme.

The null hypothesis is therefore that the dental health (measured by d_3_mft score) of children in the fluoride varnish arm of the study is no better after 18 months of varnish application than that of the children in the TAU arm. The alternative to the null hypothesis is that there will be a significantly lower increase in the d_3_mft scores of children in the fluoride varnish arm than that found in the d_3_mft of children in the TAU arm.

### Study objectives

The objective of this study is to compare the effectiveness of Duraphat fluoride varnish plus treatment as usual (TAU) with TAU only in preventing any further dental decay. The primary endpoint for each individual child is whether or not there has been any occurrence of new caries lesions over the 2 year period, as measured by any increase in d_3_mft at 2 years of follow up compared to the d_3_mft at baseline (d_3_mft is dental decay as measured by the dmft scale in the dentine).

## Methods/Design

This protocol was peer reviewed by the national evaluation board of the Childsmile Programme, which was set up by the funder (Scottish Government) to have oversight of all research and evaluation that is associated with the programme. The design is described diagramatically in Fig. 1.

**Fig. 1 Fig1:**
[figure not shown]
Flow diagram of the PT@3 Study

### Study population

Eight hundred five children will be recruited into each of the two arms of the study. They will be identified in approximately 50 nursery schools in the NHS Lothian, Greater Glasgow and Clyde, Fife and Tayside Health Board areas. Nursery schools selected for this study will serve children likely to be at a higher than average risk of caries (e.g., because the nursery school serves a population from postcode areas with a SIMD score indicating higher social deprivation). The sample is 3-year-olds attending participating nursery schools. Eligibility regarding absence of contraindications will be assessed by enquiries to parents and schools prior to study entry. Routine Childsmile information on fluoride varnish will be used, as well as the study information from a specially designed ‘participant information sheet’ (PIS).

Eligible participants will be randomised (1:1) to receive Duraphat ® fluoride varnish plus TAU or TAU only. Randomisation will follow the baseline dental examination by a study dental practitioner, and will take place via a telephone call to the Interactive Voice Response System (IRVS) at the Robertson Centre for Biostatistics, University of Glasgow. Blocks of four and two will be used within each nursery school, so that for every four/two children each of the two treatments will be allocated equally. Because the blocking is done at each nursery separately we will not necessarily complete the last block at each of the schools (i.e., when the target number of subjects in each treatment group has been reached). Members of the Extended Duty Dental Nurse (EDDN) teams undertake the randomisation of participants and are allocated a Personal Identification Number (PIN) by the RCB and trained in the use of the IVRS.

### Inclusion criteria

Provision of a signed informed consent form from a parent or legal guardian.Children in the first year of nursery school (known as the ‘ante pre-school year’).Every eligible child in participating nurseries will be invited to join the study, irrespective of the SIMD ranking of their own postcode.Children with or without pre-existing cavities, as the cavity can be treated through the usual primary care dental service (i.e., as part of ‘treatment as usual’).

### Exclusion criteria

Children with contraindications for the Duraphat varnish i.e., hypersensitivity to colophony and/or any other constituents.A history of bronchial asthma requiring hospitalisation.History of allergic episodes requiring hospital admission.

### Identification of participants and consent

Once the head teacher has given permission, an information sheet and consent form will be given or sent to the parents or guardians of every ante pre-school child. The participant information sheet makes clear the duration of the trial and that participation is voluntary and that the parent or guardian can withdraw their child at any point. Child home postcodes from the school registration rolls will be linked to the Scottish Index of Multiple Deprivation (SIMD) to ensure any potential participation bias can be analysed, and to ensure outcomes can be assessed by deprivation.

Children will not be approached for consent/assent due to their young age. Informed consent will be obtained directly from the parents/guardians by members of the study team at their child’s nursery, at the consenting visit which will take place at least 24 h after the distribution of the PIS. Trial staff will also ask consenting parents and guardians to complete a contraindications checklist (adapted from the Childsmile Consent Form for Toothbrushing & Fluoride Varnish [version 7.1]). The checklist will screen children for the contraindications for Duraphat® varnish (listed above). All checklists with information on possible contraindications will be assessed to decide if the child should be excluded from the trial. On the day of the dental inspection any child showing distress or verbal or non-verbal signs of extreme reluctance will be excluded from the study if the dentists feel that continuing with the inspection would cause the child further distress.

### Withdrawal of subjects

Immediately prior to the 6, 12, and 18 Month interventions, parents/guardians will be requested to update information on contraindications to Duraphat® varnish. Parents/guardians will be sent a self-complete version of the Contraindications checklist (adapted from the Childsmile Consent Form for Toothbrushing & Fluoride Varnish [version 7.1]) and a covering letter. The checklist will again screen children for the contraindications for Duraphat® varnish listed above. The covering letter makes it clear that the checklist must be returned if the child has developed any contraindications in the period following the previous intervention, so we can exclude that child from the intervention. All returned checklists will be assessed by the trial dentist who will decide if the reported contraindication for Duraphat® varnish requires that the child be withdrawn from the study.

Parents who withdraw their child will be asked, if appropriate, to agree to their having the end-of-study dental examination, in order to make best use of information already collected on that child. Children who leave a trial nursery school during the study, but remain in the local area, and go on to attend a local primary school will receive an endpoint dental inspection. The parents/guardians of these children will be informed of the inspection.

Any adverse reactions to the fluoride varnish (e.g., mucositis, allergic reaction etc.), whether noted by Childsmile staff or reported by parents or school, will be entered into the Case Report Form by the study dental nurse or dental health support worker. All recorded adverse reactions will be reviewed by the site Principal Investigator. Details of adverse reactions will be assessed against the criteria for expedited pharmacovigilance reporting to the MHRA and Research Ethics Committee. If any immediate adverse reaction is suspected, the varnish can be easily removed by toothbrushing, rinsing and spitting. Any child with a suspected immediate adverse reaction will be permanently withdrawn from the study.

### Study schedule

Up to six visits are involved for children who are retained throughout the study. The first will be to complete the baseline dental inspection. This is followed by randomisation and the first of four intervention/TAU visits by the study Childsmile team to the nursery school, spaced roughly six months apart. The final visit is to undertake an endpoint dental inspection to re-inspect the child in year 1 of their primary school. Neither children nor parents are required to make special visits to a clinic or other study base. Where possible, visits 1 and 2 will be combined: i.e., if logistics allow, the first varnish/TAU intervention will be completed after the baseline dental examination and the subsequent randomisation.

#### Visit 1/visit 2: Examination/randomisation/0 month intervention visit(s)

At this visit study staff will confirm eligibility before the baseline dental examination is carried out by a study dental practitioner (e.g., signed consent form is in place, enquiry form regarding contraindications is complete and the child has no obvious temporary infections or injuries which would lead to exclusion on the day). Completion of CRF containing dental examination data.

All children receive treatment as usual (TAU), namely supervised toothbrushing in the nursery. Randomisation will take place via a telephone call to the IRVS at the Robertson Centre for Biostatistics. As soon as possible following randomisation, the study Childsmile team will perform a brief oral check, depending on randomisation they either get a “sham” fluoride varnish application (applicator brushing teeth with no fluoride varnish on it) or they get the active treatment involving application of fluoride varnish. The dental nurse will record treatment arm in order to ensure consistency of treatment throughout the sequence of visits.

#### Visit 3: 6 Month (+/- 3 months) intervention visit to nursery school

In the week prior to the visit parents will be sent the contraindications checklist and covering letter (detailed above). If the parents are aware of any contraindications this checklist will be returned to the nursery school. On arrival at the nursery school the study dental team will ascertain if any checklists have been returned. If no exclusion criteria are identified, the study dental team will again either apply fluoride varnish, or deliver TAU, including a brief oral check, as dictated by the original study arm allocation. As before, children with temporary conditions (e.g., cold sores, abrasions, or systemic illnesses) will not have FV applied, but will remain in the study. Children absent at this or subsequent visits will also continue in the study unless actively withdrawn by a parent or following assessment of any adverse reaction.

#### Visit 4: 12 Month (+/- 3 months) intervention visit to nursery school

Procedures as for Visit 3 above.

#### Visit 5: 18 Month (+/- 3 months) intervention visit to nursery school

Procedures as for Visit 3 above. If necessary, this visit may take place in the first term of the child’s first year in Primary school. Relevant school staff will be informed if this required.

#### Visit 6: 24 Month (+/- 3 months) end of study dental examination visit to primary school

This visit will be conducted when participating children are in Primary One, and 5 years old on average. The final dental examination will be carried out, regardless of whether or not the sequence of varnish applications or TAU contacts had been interrupted or discontinued for any reason.

#### Unexpected end of study visit

In the event of a child having to leave the study due to withdrawn consent, or moving home and so on, the head teacher of the school will inform the study team. If the parent agrees, arrangements will be made to complete the end-of-study dental inspection in order to maintain that child in the study database.

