### Statistics and data analysis

#### Statistical analysis plan

The study will have a comprehensive Statistical Analysis Plan, which will govern all statistical aspects of the study, and will be authored by the trial statistician and agreed by the Trial Management Group (TMG) before any unblinded data is seen.

Binary endpoints such as evidence of any new decay will be analysed by Mantel-Haenszel Chi-squared tests and odds-ratios, with the attendant 95 % confidence intervals. This type of analysis will also be carried out on safety event data. Changes in d_3_mft will be analysed by Wilcoxon tests, unless these changes are normally distributed and therefore suitable for analysis by Analysis of Covariance. Compliance will be compared with a chi-squared test. The subgroup analyses will be carried out for the primary endpoint using logistic regression with interaction terms between treatment and subgroup. All statistical tests will be two-tailed tests at the 5 % significance level. There should be no concerns regarding multiple testing. All randomised controlled trials examine secondary endpoints to examine consistency of results and to generate hypotheses for further research.

All analyses will follow the intention to treat principle [8, 11]. Study subjects will be analysed in their randomised groups regardless of the treatment actually received. Also, subjects who violate the rules of the study (‘protocol violators’) will be included in all of the analyses, provided that the 2 year endpoint data has been recorded. Ideally an intention to treat analysis would be carried out on all of the randomised subjects, but there is usually some missing primary endpoint data that prevents this. We will also carry out a ‘Worst Case Analysis’ of the Primary Endpoint. In this analysis the missing endpoints will be assumed to be treatment failures, e.g., ‘new decay’.

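### Withdrawal from the study after a suspected reaction does not fit the 24-month examination or intention to treat, and the leavers' end-of-study inspection is untimed

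*Protocol article*

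**What the plan says.** **The general rule is retention.** The Visit 6 section says: "The final dental examination will be carried out, regardless of whether or not the sequence of varnish applications or TAU contacts had been interrupted". The sentence goes on to cover discontinuation for any reason, and the visit is set at 24 months +/- 3 months. The Treatment section keeps children who miss some or all treatments and contacts. The Visit 3 section keeps absent children, except after active parental withdrawal or the assessment of an adverse reaction. Withdrawal of subjects gives children who leave the nursery but stay local an endpoint inspection in primary school.

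**Withdrawal rules.** The same section says: "Any child with a suspected immediate adverse reaction will be permanently withdrawn from the study". For a newly reported contraindication, returned checklists go to the trial dentist "who will decide if the reported contraindication for Duraphat® varnish requires that the child be withdrawn from the study", although the covering letter gives its purpose as "so we can exclude that child from the intervention". For parental withdrawal: "Parents who withdraw their child will be asked, if appropriate, to agree to their having the end-of-study dental examination".

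**Leavers.** A separate section, Unexpected end of study visit, opens with these triggers: "In the event of a child having to leave the study due to withdrawn consent, or moving home and so on". Once the study team has been informed, and with parental agreement, "arrangements will be made to complete the end-of-study dental inspection in order to maintain that child in the study database".

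**Analysis.** The primary endpoint is any increase in d3mft at 2 years over baseline. Children are analysed as randomised, whatever treatment they received. Protocol violators are included "provided that the 2 year endpoint data has been recorded". A worst-case analysis counts missing endpoints as new decay.

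**The concern.** The first problem is a contradiction. Site staff who permanently withdraw a reacting child from the study cannot also follow the rule that the final examination takes place whatever ended treatment. The protocol describes a route to the final examination when a parent withdraws a child, but none when staff do. A suspected immediate reaction to varnish presupposes that varnish was applied, so the loss falls in practice on one arm and is caused by treatment. This is the kind of loss that an intention-to-treat analysis is meant to avoid.

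The second problem is a gap. The leavers' inspection has its own heading, apart from Visit 6, is triggered by departure, and is meant to keep the child in the database. If it takes place at month 6 or 12 and is entered as the endpoint, a child with no new decay by then is scored as free of new decay over 2 years. That understates decay in both arms and shrinks the absolute difference. If leaving differs by arm, it biases the comparison. Such a child would also escape the worst-case analysis, because the endpoint would not be missing.

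**Working it through.** **Part 1: the withdrawal rules side by side**

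| Situation | Where | Outcome for the child |
|---|---|---|
| Treatment interrupted or discontinued, any reason | Visit 6 | Final examination done |
| Treatments or contacts missed, even all | Treatment | Retained |
| Parent withdraws child | Withdrawal of subjects | Asked, if appropriate, to allow the final examination |
| Suspected immediate reaction | Withdrawal of subjects; exception repeated in Visit 3 | Out of the study; no examination mentioned |
| New contraindication | Withdrawal of subjects | May leave the study; the letter speaks only of the intervention |

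The fourth row conflicts with the first. The fifth row is inconsistent within its own section. Checklists go to parents in both arms, so contraindication withdrawals are not confined to varnish. Reaction withdrawals in practice are.

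Size: if a share w of the varnish arm is removed, the observed rate moves by w x (risk in those left - risk in those removed). With w = 1% (assumed), this cannot exceed 1 point. Power with 478 varnish children instead of 483 is 89.9%.

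**Part 2: the untimed inspection**

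*The plan's own figure.* Inputs from Sample size: 0.41 v 0.31, two-sided alpha 0.05, power 90%, dropout 40%. The pooled chi-squared formula without continuity correction gives 483 per group (power 90.05%), and 483 / (1 - 0.40) = 805. Both figures reproduce, so the point rests on the text and not on a wrong sample size.

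*Assumptions.* The article gives neither the share of children inspected early (e) nor the month (m). Both are assumed equal in the two arms unless stated. Two accrual models are used:

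- Linear: observed rate = p x [1 - e x (1 - m/24)].
- Constant hazard: risk at month m = 1 - (1 - p)^(m/24); observed rate = (1 - e) x p + e x risk at m.

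For e = 20%, m = 12:

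- Linear: 0.41 x 0.90 = 0.369 and 0.31 x 0.90 = 0.279, a difference of 9.0 points.
- Constant hazard: risks at month 12 are 0.2319 and 0.1693. Then 0.8 x 0.41 + 0.2 x 0.2319 = 0.3744 and 0.8 x 0.31 + 0.2 x 0.1693 = 0.2819, a difference of 9.25 points (9.3 rounded).

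| e | m | Linear difference | Constant-hazard difference | Power at 483 per arm (constant hazard) |
|---|---|---|---|---|
| 5% | 12 | 9.75 | 9.8 | 89% |
| 20% | 12 | 9.0 | 9.3 | 87% |
| 20% | 6 | 8.5 | 8.7 | 83% |
| 40% | 12 | 8.0 | 8.5 | 83% |

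With equal shares under linear accrual the risk ratio does not change: 0.279 / 0.369 = 0.31 / 0.41 = 0.756. The dilution is in the absolute difference.

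*Unequal shares, no true effect.*

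- Linear, m = 12, early shares 15% (control) and 25% (varnish): 0.41 x 0.925 = 0.379 and 0.41 x 0.875 = 0.359, a false benefit of 2.05 points.
- Constant hazard, 5% of the varnish arm only, m = 6: 0.05 x (0.41 - 0.1236) = 0.0143, a false benefit of 1.4 points.

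**The case against.** **Retention is the norm.** A reader might infer that children who stop early are, as a rule, either inspected early or lost. The documents do not support that. Most children who stop treatment are kept and examined at 24 months. This stands, and limits the point to the two exceptions.

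**An early inspection is not said to be the endpoint.** The leavers' section gives no date and speaks only of keeping the child in the database. The endpoint is fixed at 2 years, and the analysis requires 2-year data, which can be read as already excluding a month-6 inspection. The SAP, which is not shown, may settle it. This stands in part. That the visit is early and counted is a fair inference from its heading and purpose, but it is not stated. The gap is that the protocol sets up the inspection without saying what it is for in the analysis.

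**Intention to treat.** An early inspection leaves the child in the randomised arm and does not breach intention to treat. This stands. Only withdrawal from the study bears on that principle.

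**Reactions are rare and the exception is deliberate.** The Background reports 168,000 applications with no reported significant adverse events, and the Visit 3 section repeats the exception. The effect will be small, but the conflict with the Visit 6 rule remains.

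**The magnitudes are hypothetical.** No early share or timing has a source in the article. Moving home has no evident link to allocation, and controls receive a sham application. Excluding early inspections can also cost power: if 20% of 483 per arm were dropped, 386 would remain and power would be about 83%, against 87% if they were counted at month 12. This stands. The case for excluding them is that they do not measure 2-year decay, not that it gains power.

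**Conclusion.** The point holds in two limited parts.

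1. Permanent withdrawal from the study after a suspected reaction, and possibly after a new contraindication, contradicts the rule that the final examination is done however treatment ended, and does not fit intention to treat. The reaction trigger is varnish-related in practice; the contraindication trigger can arise in either arm. The expected effect is small, at most 1 point if 1% of the varnish arm were lost.

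2. The leavers' inspection has no timing and no stated role in the primary analysis. If inspections well before month 21 were counted, new decay would be understated. With 20% inspected at month 12, the difference would be 9.0 to 9.3 points instead of 10. Unequal shares could create a false difference of about 1.4 to 2 points in the examples shown. All of these figures rest on assumed shares, timings and accrual models.

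The documents do not show that bias will occur or that early inspections will be scored as 2-year outcomes. They do leave both possible, and a few sentences would close them off.

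**What to change.** - Reconcile Withdrawal of subjects, the Visit 3 and Visit 6 sections, Unexpected end of study visit, Treatment, and the Statistical analysis plan section, so that leaving the application or contact schedule is separate from leaving follow-up. State that the 24-month examination is sought for every randomised child unless the parent refuses, including any child already inspected on leaving.
- State that only inspections at 21 to 27 months, the Visit 6 window, count as the primary endpoint. Treat a child with only an earlier inspection as missing at 2 years, and so covered by the planned worst-case analysis. Use the early inspection in a sensitivity analysis only.
- If the SAP already says this, align the protocol text with it before unblinded data are seen.

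The cost is a few sentences and a somewhat smaller complete-case set. The sample size need not change: it already allows for 40% without an endpoint (805 x 0.60 = 483), provided early-inspected leavers fall within that 40%. No change to when varnish is stopped is proposed.
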